##### Anthropometric measures

The baseline anthropometric measures (i.e., height and body mass) will be self-reported by the participants due to the impossibility of virtual assessment.

##### Follow-up questionnaire

An adaptation in the questionnaire used in Schott et al. [47] was made to evaluate important outcomes in cancer patients such as safety, fun, motivation, future, benefits for daily life, intervention partner influence, training-related exhaustion, satisfaction, self-confidence on physical performance, supervision preference, changes in lifestyle including physical activity and eating habits, and main barriers to group participation. Participants will answer 14 questions about the individual perception of the intervention using a 7-point Likert scale from 1 (i.e., do not agree at all) to 7 (i.e., I entirely agree). The follow-up questionnaire is available in Additional file 0^2^.

##### Adherence assessments

Adherence is recorded as group attendance and compliance in both interventions. Adherence will be treated by absolute and relative frequency of the number of sessions performed. Compliance will be treated as the number of sessions in which the full protocol was achieved.

#### Data management

Questionnaires data will be collected by online forms (Google Forms), and the functional performance test scores will be filed on a Google Sheet. All data will be stored in the Google Drive linked to a specific email for the trial that only researchers involved have access to. Data entry is carried out for two investigators individually ([name] and [name]) and will remain in their ownership. Audition for missing or inaccurate data will be conducted when necessary.

#### Statistical considerations

Generalized Estimating Equations (GEE) and Bonferroni post hoc tests will be used for comparison between time points (baseline and post-intervention) and groups (MTHE and HE) for both per-protocol and intention-to-treat analyses. The per-protocol analysis (PP) will count all women with training frequency ≥ 70% of intervention sessions (≥ 16 sessions for participants allocated in the exercise program, and ≥ 8 sessions for participants allocated to the education program). For the intention-to-treat analyses, the incomplete data (i.e., missing values) will be estimated using maximum likelihood estimation by the automatic regression imputation method.

Additionally, we plan to carry out subgroup analysis stratifying both groups by clinical characteristics of the tumor (histological type of tumor, tumor staging, and status of hormone receptors) and treatment (chemotherapy and radiotherapy protocols). Considering that withdrawals may occur due to specific harms or other non-anticipated reasons, we will assess whether additional grouping (indicator) should be made due to different missing data patterns. Therefore, we will qualitatively document reasons and details of withdrawals on a case-by-case basis. Continuous variables will be summarized according to intervention groups at baseline, if applicable, and end of trial using arithmetic or geometric means, standard deviations, ranges, and interquartile ranges as appropriate. According to intervention groups, categorical variables at baseline and end of the trial (if applicable) will be summarized as absolute number and proportion of subjects (%). Standardized effect sizes will be calculated by dividing the between-group difference of the post-intervention means by the pooled baseline standard deviation. The significance level established for all analyses will be *p* < 0.05, and all statistical procedures will be analyzed and processed using the SPSS version 22.0 software.

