**Methods:**

This study is a randomized controlled trial. Women undergoing primary treatment (during or after chemotherapy) for breast cancer (stages I–III) will be randomly assigned to MTHE (twice a week) or HE (once a week). MTHE components are mobility, aerobic, balance, resistance, and flexibility home-based exercises, supervised by video call. The primary study outcome is cancer-related fatigue. The secondary outcomes are quality of life, symptoms of depression and anxiety, physical activity level, cancer-related cognitive impairment, and functional capacity. Other outcomes are adherence to interventions and a follow-up questionnaire evaluating the individual perception in motivation, lifestyle changes, and main barriers to participation. All outcomes will be remotely assessed before and after intervention. Our analysis will follow the intention-to-treat approach and per-protocol criteria, with additional sub-group analysis.

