#### Sample size

The sample size estimation was based on the number of patients feasible to collect given our financial resources during the period of the study (concomitant with the COVID-19 pandemic )[29]. We estimate that the total sample will be around 30 participants. Therefore, approximately 15 women will be enrolled in each group.

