#### Assignment of interventions and blinding

After consent, each participant will receive an internal identifier number. After completing the baseline assessments, participants are randomized to either the MTHE or HE. A blinded investigator created a computer-generated randomization sequence, via random function (Excel software), 1:1 ratio, with a block of random sizes that are not disclosed to ensure concealment. The allocation concealment is implemented by researchers in charge of requesting randomization for one of the blind investigators with access to the randomization list ([name], [name]), via email, from the identifier number. A researcher ([name]) allocates individuals in the groups by phone call or WhatsApp message. Randomization requests follow the order in which participants complete the baseline assessments. The allocation date of the participants is recorded in an Excel spreadsheet.

Blinding will be applied for assessors of all primary and secondary outcomes, except physical activity level and cognitive function (the researcher monitoring these two evaluations is not blinded, but both questionnaires are self-administered). Participants are asked to omit their assigned group and not talk about their interventions during the outcome assessments. Due to the nature of the intervention, the study staff supervising training sessions and participants are non-blinding. In unblinding cases, the principal investigator will be notified with the participant ID, date, and reasons for unblinding.

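### GEE at p < 0.05 with about 15 women per arm names no small-sample correction; the standard large-sample Wald tests would run at about 6% to 7%, not 5%

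*Protocol article*

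**What the plan says.** The Statistical considerations section of the protocol article fixes the method: "Generalized Estimating Equations (GEE) and Bonferroni post hoc tests will be used for comparison between time points (baseline and post-intervention) and groups". The same sentence applies it to both the per-protocol and the intention-to-treat analyses. The section also fixes the level, "The significance level established for all analyses will be *p* < 0.05", and the software, "all statistical procedures will be analyzed and processed using the SPSS version 22.0 software".

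The Sample size section sets the number of women by feasibility: "We estimate that the total sample will be around 30 participants", so that "approximately 15 women will be enrolled in each group". Allocation is 1:1 (Assignment of interventions and blinding). There are two measurements per woman; the Abstract says "All outcomes will be remotely assessed before and after intervention".

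Two further parts of the plan use fewer women. "The per-protocol analysis (PP) will count all women with training frequency ≥ 70% of intervention sessions", and subgroup analyses split both arms by tumour and treatment characteristics.

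The article does not say whether the GEE variance is robust or model-based, which reference distribution the tests use, or whether any small-sample correction applies.

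**The concern.** The usual GEE test divides an estimate by a large-sample standard error and refers the square to chi-square. Both steps rely on many independent participants, and here there are about 30. Two things go wrong, in the same direction. The uncorrected sandwich variance is multiplied by (n-1)/n, so it is about 1/n too small. The chi-square reference also ignores the fact that the variance is estimated.

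The consequence is a true error rate above the stated 5%, in a trial whose hypothesis is superiority on the primary and secondary outcomes. The size was set by resources, so the sample cannot be expected to grow out of the problem.

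**Working it through.** The article has no power calculation to reproduce, so the figure tested is the nominal level of 0.05.

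**Inputs from the protocol article.** 15 women per arm, 1:1 allocation, two time points, GEE on group and time, level 0.05.

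**Assumptions.** Two-sided tests; complete data; normal outcome; a model with group, time and their interaction; Wald tests on 1 degree of freedom with no correction.

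**Step 1: the estimate and its sandwich variance.** With two time points and complete data, the GEE interaction estimate is the difference between arms in mean change. Within an arm of n women, with s² the usual unbiased variance of change, the uncorrected sandwich uses ((n-1)/n) × s²/n in place of s²/n. At n = 15 the factor is 14/15 = 0.933, so the variance is 1/15 = 6.7% too small.

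**Step 2: the true level.** The Wald statistic equals t × √(n/(n-1)), with t on 2n-2 degrees of freedom. The test rejects when |z| > 1.96, that is, when |t| > 1.96 × √((n-1)/n).

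At n = 15 the effective cut-off is 1.96 × √(14/15) = 1.96 × 0.966 = 1.893, and P(|t₂₈| > 1.893) = 0.0687. The correct cut-off is 2.048. An interval from the uncorrected sandwich has 1.893/2.048 = 0.924 of the correct width, which is 7.6% too narrow, with 93.1% coverage.

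**Step 3: model-based variance.** If the variance of change is estimated without bias, only the reference distribution is wrong: P(|t₂₈| > 1.96) = 0.060. This figure depends on how the software scales the working correlation. In 4,000 fitted GEE runs with a model-based variance, one package rejected in 7.5%. A different divisor could bring the figure closer to nominal.

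**Step 4: smaller sets.** The article gives no per-protocol or subgroup sizes, so the sizes below 15 are assumptions.

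| Women per arm | Sandwich, chi-square | Unbiased model-based, chi-square |
|---|---|---|
| 15 (planned) | 6.9% | 6.0% |
| 12 (assumed) | 7.4% | 6.3% |
| 10 (assumed) | 7.9% | 6.6% |
| 8 (assumed) | 8.8% | 7.0% |
| 5 (assumed) | 11.8% | 8.6% |

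**Step 5: checks by simulation, 15 per arm, sandwich with chi-square.**
- The simulated form of the formula gave 6.9% (0.0695 in 200,000 runs).
- Skewed data gave 6.6%.
- Unequal SDs (ratio 1.5) gave 6.9%.
- Fitted GEE models with exchangeable correlation gave 7.1%, and 7.0% with 20% of follow-up values missing.

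**Step 6: does a correction restore the level?** Unbiased variance with t on 28 degrees of freedom gave 5.05% in simulation, and 4.7% with skewed data. A bias-reduced sandwich with the same t reference in fitted GEE gave 4.0%, or 4.2% with 20% missing, so it is slightly conservative.

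**Step 7: Bonferroni.** If six pairwise comparisons are made (assumed), the nominal per-test level is 0.05/6 = 0.0083. The formula in Step 2 with that cut-off gives 0.0166 at 15 per arm. The Bonferroni bound is then 6 × 0.0166 = 0.0995, not 0.05.

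**The case against.** The strongest reply is that the article never specifies the procedure being criticised. It names GEE and nothing about the sandwich, chi-square or degrees of freedom. Those details often sit in a statistical analysis plan, and one not shown here may contain a correction. GEE with a corrected variance and t reference holds the level, so naming GEE is not itself an error. This stands to the extent that every figure above is conditional on uncorrected tests. It does not remove the point. The article fixes the method, the level and the sample size together, and run in its ordinary form that method misses that level.

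A second reply is that 6.9% is not far from 5%. That is fair for the intention-to-treat comparison, where the excess is 1.9 percentage points. The larger figures belong to set sizes the article does not give, and the subgroup analyses are additional.

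A third is that Bonferroni protects the post hoc tests. A single adjusted comparison, at about 1.7%, does stay well below 5%. Bonferroni corrects for the number of tests, though, and not for the level of each. With six assumed comparisons each test runs at about twice its nominal level, and the family-wise bound is about 10%.

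A reader might also infer that the 5% level is certainly broken, or that every confidence interval in the trial will be too short. The document supports neither. The estimator is unstated, and the Statistical considerations section plans p-values, summaries and standardized effect sizes but no confidence intervals.

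**Conclusion.** The point holds in conditional form and is worth correcting. If the tests are uncorrected large-sample Wald tests, the group-by-time test at 15 per arm has a true two-sided level of about 6.9% with the sandwich variance, or about 6.0% with an unbiased model-based variance. The excess is modest for the main comparison. It is larger in the per-protocol and subgroup analyses, by an amount that depends on sizes the article does not give. The figures rest on complete, normal data, but they changed little with skewness, unequal SDs or 20% missing follow-up. They leave out any effect of the planned imputation. If a correction is already specified elsewhere, confirming it settles the matter.

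**What to change.** For the continuous outcomes, choose one of these and state it:

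- Keep GEE, with a small-sample corrected sandwich variance and a t or F reference in place of chi-square.
- Use a REML mixed model with Satterthwaite or Kenward-Roger degrees of freedom. This keeps the planned comparisons between time points.

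A baseline-adjusted linear model with a t test also serves for the between-group contrast, but it does not by itself give the time-point comparisons. The same choice should cover the per-protocol and subgroup analyses, where it matters more. The sponsor should confirm that the chosen software version offers the correction, or name another.

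The cost is a few lines of analysis wording and slightly larger p-values. Design, recruitment and data collection do not change.

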### Primary outcome

The primary study outcome is cancer-related fatigue, which will be assessed using the Piper fatigue scale. Cancer-related fatigue was chosen as the primary outcome because it is a widespread side effect caused by chemotherapy, and it is identified among high-priority cancer- and treatment-related toxicities based on its potential to affect cancer care rapidly [28, 38].

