#### Data collection

On the first day, previous physical activity levels and cognitive function will be assessed. After at least a 48-h interval from the first day, primary and all other secondary outcomes will be measured. During the assessments a video call (Google Meet) will be held with each participant individually. The evaluators were trained before starting the trial, and periodic meetings and written communication between the evaluators will be established fortnightly to promote internal transparency and consolidate data collection procedures. The time scheme for study conduction is presented in Table 2.

**Table 2 Tab2:** Time scheme for ABRACE: Telehealth conduction

Study period							
	Enrolment and baseline measures	Baseline measures	Allocation	Post-allocation		Close out	
**Timepoint**	**t**_**0**_	**t**_***1***_	***t***_***2***_	***t***_***3***_	***t***_***4***_	***t***_***5***_	***t***_***6***_
Timepoint description	Interview and baseline evaluations day 1	Baseline evaluation day 2	-	Intervention start	Intervention end	Final evaluation day 1	Final evaluation day 2

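### The planned GEE treats baseline fatigue as an outcome and names no baseline adjustment, giving up precision that a score collected before randomization would supply at almost no cost

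*Protocol article*

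**What the plan says.** Under Primary outcome the article states: "The primary study outcome is cancer-related fatigue, which will be assessed using the Piper fatigue scale". Under Statistical considerations it gives the analysis in one sentence, as GEE with Bonferroni post hoc tests for "comparison between time points (baseline and post-intervention) and groups (MTHE and HE) for both per-protocol and intention-to-treat analyses". Baseline is therefore a category of time, on the response side of the model. The section names neither a covariate nor a constraint on the baseline means, and it does not name the group-by-time term. It defines the standardized effect size as the between-arm difference in post-intervention means over the pooled baseline SD, again without baseline adjustment.

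The timing is clear. Assignment of interventions and blinding says: "After completing the baseline assessments, participants are randomized to either the MTHE or HE". Table 2 agrees, with fatigue at t1, allocation at t2 and final fatigue at t6.

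The Sample size section bases the number on feasibility: "We estimate that the total sample will be around 30 participants", and so "approximately 15 women will be enrolled in each group". The article gives no target difference, SD, power or baseline-to-post correlation.

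**The concern.** Because baseline fatigue is measured before randomization, the two arms have the same expected baseline mean. A model that gives each arm its own baseline mean does not use that fact. With two time points its group-by-time contrast subtracts the whole observed baseline difference. The post-intervention contrast subtracts none of it. Baseline adjustment subtracts the fraction that the data show to carry over to the final score.

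Two things are at stake. The first is precision in a trial of about 30 women whose size was set by resources. The second is coherence: the group-by-time estimate and the planned effect size differ by exactly the chance baseline difference, so they can tell different stories about the same data. Naming the group-by-time term as the primary contrast would not by itself cure either problem.

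**Working it through.** **Inputs from the article.** About 15 women per arm, N = 30, 1:1 allocation, two time points, significance level 0.05 (taken as two-sided, since sidedness is not stated). There is no power calculation to reproduce.

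**Assumed, not in the documents.** Baseline-to-post correlation r = 0.3, 0.5, 0.7, with 0.9 as a check; equal variance σ² at both times; complete data. σ cancels from every ratio below.

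**Step 1: what the GEE estimates.** A GEE with arm, time and their interaction, fitted to simulated data with 15 per arm, gave an interaction of 0.438 under both independence and exchangeable working correlation. The difference in mean change in the same data was 0.438. They are the same estimator.

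**Step 2: variances** (n per arm).
- Group-by-time (change): 2σ²(1 − r) × 2/n
- Post-intervention only: σ² × 2/n
- Baseline-adjusted (ANCOVA): σ²(1 − r²) × 2/n in large samples, multiplied by (N − 3)/(N − 4) = 27/26 for estimating the slope at N = 30

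**Step 3: loss of the group-by-time contrast against adjustment.** The variance ratio is (1 − r²)/[2(1 − r)] = (1 + r)/2, so the large-sample loss is (1 − r)/2. At N = 30 the loss is 1 − (27/26)(1 + r)/2.

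| r | Large-sample loss | Loss at N = 30 | Large-sample SE reduction, 1 − √((1 + r)/2) | Equivalent N, 30/(1 − loss at N = 30) |
|---|---|---|---|---|
| 0.3 | 35% | 32.5% | 19% | 44 |
| 0.5 | 25% | 22.1% | 13% | 39 |
| 0.7 | 15% | 11.7% | 8% | 34 |
| 0.9 | 5% | 1.3% | 3% | 30 |

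The last column is the number of women that a change-score analysis would need to match 30 analysed with adjustment. Simulation (20,000 trials, 15 per arm) gave losses of 32.3%, 22.2% and 12.1% at r = 0.3, 0.5 and 0.7. Break-even at N = 30 is where (1 + r)/2 = 26/27, that is r ≈ 0.93.

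**Step 4: loss if the post-intervention contrast is used.** In large samples it is 1 − (1 − r²) = r²: 9%, 25% and 49%. At N = 30 it is 1 − (27/26)(1 − r²): 5.5%, 22.1% and 47.0%.

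**Step 5: chance imbalance.** The baseline difference between arms has standard error √(2/15) = 0.37 SD. At r = 0.5, an imbalance of that size makes the change contrast over-correct by (1 − 0.5) × 0.37 ≈ 0.18 SD. The post-only effect size under-corrects by 0.5 × 0.37 ≈ 0.18 SD.

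**Step 6: illustrative power.** For an assumed true difference of 0.8 SD at 15 per arm, a t test on change (28 df) against ANCOVA (27 df) gives 43% and 58% (r = 0.3), 56% and 67% (r = 0.5), 78% and 83% (r = 0.7). These are t-test and ANCOVA values, not the power of the planned GEE. The interaction tested with an uncorrected robust-SE Wald statistic (an assumption, since the article does not name the test) had simulated power of 49%, 62% and 82%, but with type I error of about 7% instead of 5%.

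**The case against.** The strongest reply is that this is one condensed sentence in a journal article. It does not name the interaction, the working correlation or the mean structure, and a plan not shown could add a covariate or a common baseline mean. An unconstrained group-by-time contrast is also a valid estimator in a randomized trial, and nothing in the article is contradicted.

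Part of this stands. The contrast is not named, so no single loss figure can be pinned on the plan. The finding concerns efficiency, not an error in a stated number. The rest does not rescue the plan. The article does fix baseline as a level of time, nothing in it points to a common baseline mean, and its one explicit between-arm quantity, the effect size, is unadjusted. At N = 30 both readings lose precision against adjustment across the assumed range of r.

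Three stronger readings are tempting, and the documents do not support them:
- **A fixed loss of 15% to 35%.** That is the large-sample variance figure at an assumed r, and the article gives no correlation.
- **A power shortfall of the planned analysis.** The pairs in Step 6 come from other tests and from an effect size that the article does not state.
- **Bias.** Over-correction is conditional on a chance imbalance, which can favour either arm. Averaged over randomizations, the contrast is unbiased.

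**Conclusion.** The concern holds as one of efficiency. As written, the fatigue comparison does not adjust for a score that the trial collects before allocation. On the group-by-time reading, the variance loss at 15 per arm is about 32% at r = 0.3, 22% at r = 0.5 and 12% at r = 0.7, and close to nothing by r = 0.9. On the standard-error scale the large-sample figures are only 19%, 13% and 8%. On the post-intervention reading the order reverses, with a large-sample loss of 9% at r = 0.3 rising to 49% at r = 0.7.

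These figures rest on the assumed correlations, equal variances at the two times and complete data. The direction does not depend on which value in the 0.3 to 0.7 range is true. The change is worth making because it is nearly free in a trial of this size, but the planned analysis is not invalid without it.

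**What to change.** Before between-arm outcomes are examined, state that the primary fatigue result is the final Piper total regressed on arm with baseline Piper total as covariate. Alternatively, keep the two-time-point model and constrain the arms to a common baseline mean. Report the adjusted difference with its 95% CI, and base the standardized effect size on that difference so that the two agree. Use the same form for each secondary outcome with its own baseline value.

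The cost is one degree of freedom per outcome and a change of wording. No new data are needed, since Table 2 already schedules the baseline scores. If power figures are quoted, label them as illustrative t-test and ANCOVA values for an assumed 0.8 SD effect.

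### Stratified subgroup tests on five factors in about 30 women, at an unadjusted 0.05, would give low-power and unreliable stratum findings

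*Protocol article*

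**What the plan says.** Statistical considerations commits to stratifying both arms by tumour and treatment characteristics: "we plan to carry out subgroup analysis stratifying both groups by clinical characteristics of the tumor", with the factors listed as "histological type of tumor, tumor staging, and status of hormone receptors) and treatment (chemotherapy and radiotherapy protocols". That makes five factors. The same section sets one threshold: "The significance level established for all analyses will be" p < 0.05. The only inferential method it names is GEE with Bonferroni post hoc tests, and it attaches these to the time and group comparisons in the intention-to-treat and per-protocol analyses.

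Sample size says "We estimate that the total sample will be around 30 participants" and that "approximately 15 women will be enrolled in each group". The basis is feasibility: "The sample size estimation was based on the number of patients feasible to collect given our financial resources". The randomisation is described as "1:1 ratio, with a block of random sizes", and no stratification factor is mentioned. The abstract's Methods paragraph places the subgroup work beside the two main analysis sets ("with additional sub-group analysis").

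The article does not call the subgroup work exploratory. It mentions no interaction test, no minimum stratum size and no adjustment across subgroups. Apart from stage (I to III, under the eligibility criteria), it does not give the number of levels per factor. It also does not give the GEE variance estimator or say which outcomes the subgroup analyses cover.

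**The concern.** Stratifying two arms of about 15 women by five factors produces many very small comparisons, each read against the same 0.05. Three things go wrong together. With 10 to 15 looks at the data, a chance finding becomes quite likely. Each look has too little power for a non-significant result to mean anything. And a contrast between a significant and a non-significant stratum does not test whether the treatment effect differs between strata, which is the question a subgroup analysis should answer.

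At stake is a published statement that the exercise programme reduces fatigue in, say, one stage or one receptor group, resting on a handful of women per arm. The main comparison between groups is not affected.

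**Working it through.** **Inputs from the article.** 30 women, 15 per arm (2 × 15 = 30, consistent); five factors; stage with three levels; alpha 0.05, taken as two-sided.

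**Assumptions.** Two to three levels per factor; factors independent of each other; level frequencies from even to 80/20; no dropout; primary outcome only, in one analysis set; one test per stratum.

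**1. Stratum size.** Two even levels: 15/2 = 7.5, so 7 to 8 per arm. Three even levels: 15/3 = 5 per arm. The smaller level of an 80/20 split: 0.2 × 15 = 3 per arm. Number of strata: 5 × 2 = 10 to 5 × 3 = 15.

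**2. Chance of at least one false positive if every test holds 5%.** Treating tests as independent, the chance is 1 − 0.95^k. This gives 1 − 0.95^10 = 40% and 1 − 0.95^15 = 54%, with 0.50 to 0.75 false positives expected. Strata built from the same 30 women are correlated, so null trials were also simulated (8,000 per scenario, at least 2 or 3 women per arm for a stratum to be tested), using a pooled t test. The chance was 29% to 45%. Together the range is about 30% to 55%.

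**3. Size of one test if GEE uses an uncorrected robust variance with a normal reference.** With n per arm, the robust variance divides by n where the t test divides by n − 1. The Wald statistic is therefore t × √(n/(n−1)), and its true size is P(|t with 2n−2 df| > 1.96 × √((n−1)/n)).

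| n per arm | cut-off for t | true size |
|---|---|---|
| 15 | 1.89 | 6.9% |
| 8 | 1.83 | 8.8% |
| 7 | 1.81 | 9.5% |
| 5 | 1.75 | 11.8% |
| 4 | 1.70 | 14.1% |
| 3 | 1.60 | 18.5% |

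Fitting actual GEE models to simulated null data (exchangeable correlation, 1,500 runs per n) gave 9.9%, 12.5% and 14.7% at n = 7, 5 and 4, in agreement.

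**4. Chance of at least one false positive with that test.** From the same simulated scenarios (range over the two minimum stratum sizes):

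| assumed factors | t test at 5% | uncorrected robust Wald |
|---|---|---|
| five two-level, even | 31% | 51–52% |
| mixed levels, some 75/25 or 80/20 | 29–33% | 53–63% |
| five three-level, even | 42–45% | 75–82% |

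With the Wald test the expected number of false-positive strata is about 1.0 to 2.0.

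**5. Power in one stratum for a 0.8 SD effect.** Normal approximation: Φ(0.8 × √(n/2) − 1.96). At n = 5: Φ(1.265 − 1.96) = 24%. At n = 7: Φ(1.497 − 1.96) = 32%.

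**6. Would five interaction tests be enough?** At a true 5% level, treated as independent, 1 − 0.95^5 = 23%. With uncorrected robust Wald heterogeneity tests the simulations gave 35% to 59%. Changing the type of test while keeping five p-values therefore only partly helps.

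**The case against.** The best defence is that this is supplementary work in a condensed article. The superiority hypothesis concerns the group comparison, and no conclusion is tied to a subgroup. Factor coding, interaction terms and minimum stratum sizes commonly sit in an analysis plan, which is not available here. The text neither states a model for the subgroups nor excludes an interaction test.

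Much of this stands, and missing detail of that kind is not the point. The point rests on what the article does fix: five named factors, stratification of both arms, one threshold for all analyses, and about 15 women per arm. An analysis plan that followed this text would inherit the problem. Testing within strata is the natural reading of stratifying the groups, but it remains a reading.

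Nor does the Bonferroni procedure answer the point, since the article ties it to the time and group comparisons and not to the set of subgroups.

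A reader might go further and infer that treatment phase (during or after chemotherapy) is the only factor built into eligibility and has been left off the list. The article does not support this. Stage I to III is also an inclusion criterion and is on the list, and phase may fall partly under the chemotherapy and radiotherapy heading.

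**Conclusion.** The concern holds in a bounded form. Followed on its natural reading, the subgroup plan carries roughly a 30% to 55% chance of at least one false-positive stratum on Piper total fatigue when each test keeps its level, and roughly 50% to 80% under an uncorrected robust Wald test, where a single test runs at about 9% to 18%. Power for a large effect is about 24% to 32% at 5 to 7 women per arm. These figures depend on the assumed two to three levels per factor, independent factors and no dropout. Dropout or the per-protocol set would make strata smaller.

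Two stronger conclusions are tempting and are not supported. One is that the subgroup test is invalid: that needs both GEE as the subgroup test and an uncorrected variance, and the article states neither. The other is that a spurious subgroup finding is the expected result or more likely than not. If tests hold 5%, the simulated chance stays at 29% to 45%. The 54% figure needs 15 tests treated as independent, and otherwise the chance passes one half only under the unstated Wald test. Even the lower range is too high for claims that cannot show effect modification anyway.

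**What to change.** Replace the within-stratum tests with a group × time × factor term in the primary-outcome model for Piper total. Limit this to one or two binary factors, chosen from those already collected and named now; hormone-receptor status is one candidate. Report the interaction estimate with a 95% interval based on a small-sample variance (t-based or bias-corrected), because an uncorrected robust interval would be too narrow for the reason shown in step 3. Label it hypothesis-generating and make no significance claims. Use the remaining tumour and treatment characteristics to describe the sample.

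The interval will be wide. With an even two-level factor there are four cells of 7.5 women, so the half-width is about 2.06 × √(4/7.5) = 1.5 SD of the change score (t on 26 df, no covariate adjustment). That shows plainly how little 30 women can say about effect modification.

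The cost is a change of wording and the loss of the stratum p-values. The main group comparison, data collection and sample size are unchanged.
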